### **Project aims**

Prevalence of HIV infections continue to rise in the UK, particularly amongst MSM and the reduction of new infections is a key component of the National Strategy for Sexual Health and HIV [1]. Recent reports on sexual health highlight the need to invest more in HIV prevention strategies [2, 3]. The Community HIV and AIDS prevention (CHAPS) policy (CHAPS is a partnership of several organisations led by the Terrence Higgins Trust) identifies post-exposure prophylaxis (PEP) as one HIV prevention strategy. Latest data shows that 59% of MSM in the South East Coast and 70% in London have heard of PEP, which is high compared to other regions [4]. Even higher levels of awareness are reported specifically in Brighton and Hove [5]. Local data from Brighton and the Mortimer Market clinics show an increase in the number people seeking PEP after sexual exposure.

The risk reduction intervention will consist of Motivational Interviewing (MI) augmented with information and behavioural skills building (informed by the Information-Motivation-Behavioral Skills Model). MI is defined as a 'directive, client-centred counselling style for eliciting behaviour change by helping clients to explore and resolve ambivalence' [6] which is particularly pertinent amongst MSM who may require a more tailored preventive strategy.

The Information, Motivation and Behavioural skills (IMB) model has been shown to provide a good basis for understanding and predicting HIV-relevant health behaviour and health behaviour change in almost two decades of research [7]. In addition, interventions based on this model have been effective in changing risky sexual behaviour among HIV negative and HIV infected individuals in more than 25 studies [8] and in changing levels of adherence behaviour amongst people with HIV/AIDS [9, 10]. The IMB has yet to be applied to a short term prophylactic regimen of medication after risky sexual exposure but its previous successful application to HIV risk reduction suggests that it is an appropriate model on which to base an intervention based on PEP. This will be the first time that a sexual risk reduction, telephone delivered intervention guided by the IMB model has been tested with individuals seeking PEP. This study will also provide estimates of the cost-effectiveness of the intervention through the inclusion of an economic evaluation.

### **Objectives and hypotheses**

The primary aim is to examine the impact of motivational interviewing augmented with information and behavioural skills building (informed by the Information-Motivation-Behavioural Skills Model), over and above usual care, on risky sexual behaviour in MSM prescribed PEP after potential sexual exposure.

A secondary aim of this research is to examine the impact of the intervention on adherence to PEP.

Specifically we hypothesize that compared with treatment/ management as usual, those in the intervention arm will:

- 1) Report a reduction in the proportion of risky sexual practices (less unprotected anal intercourse (UAI) (receptive and insertive), increased use of condoms, a reduction in partners);
- 2) Have greater levels of adherence to PEP treatment;
- 3) Have lower rates of need (subsequent use) of PEP;
- 4) Have greater motivation to avoid risky sexual behaviours;
- 5) Have greater knowledge of risk reduction strategies;
- 6) Have greater risk reduction behavioural skills;
- 7) Have lower incidences of anal gonorrhoea;
- 8) Have lower incidences of HIV.

## Background

Post-exposure prophylaxis following sexual exposure (PEPSE) to the human immunodeficiency virus (HIV) has been recommended as a method of preventing HIV infection in the UK [11]. Recommendations for treatment are derived from the existing use of antiretrovirals to prevent HIV infection after high risk occupational exposure to the virus ('needle-stick injuries') [12]. Recommendations for prescribing PEP result from the clinician's assessment of risk of transmission. If the risk of HIV transmission through particular sexual practices is of a similar magnitude as occupational exposures (such as unprotected anal intercourse and receptive oral sex) then PEP should be recommended [13].

Evidence suggests that PEP may reduce the risk of HIV infection if given within 72 hours and adhered to rigorously for 28 days [12, 14, 15]. Sustained adherence is required to prevent treatment failure, however, non-adherence of a quarter to a third of those prescribed it has been reported [5, 16]. The treatment can be challenging to patients due to side-effects such as diarrhoea, nausea, headaches and vomiting, and is costly.

Men who have sex with men (MSM) are the group most affected by the HIV epidemic in the UK [17] and their sexual risk taking behaviour is reported to be increasing [18, 19]. As part of a comprehensive strategy across HIV prevention and care, behavioural interventions remain an important tool in the global fight against HIV [20]. One to one behavioural interventions, such as motivational interviewing (MI) have been recommended [21, 22] to reduce HIV in high risk groups. NICE guidance places recommendations for one to one interventions within the context of current STI/HIV service provision [1, 23] and states that these interventions are integral to the modernisation of sexual health services [22].

Similar to repeat testers for sexually transmitted infections (STI's) and HIV, seeking PEP after potential sexual exposure may indicate an unmet prevention need and provides an opportunity to target interventions thus potentially lowering the likelihood of further risk behaviour [24, 25].

We will establish a telephone-administered intervention based on motivational interviewing (MI) augmented with information and behavioural skills building (informed by the Information-Motivation-Behavioral Skills Model). MI is defined as a 'directive, client-centred counselling style for eliciting behaviour change by helping clients to explore and resolve ambivalence.' [6]. It is viewed as particularly useful for individuals who are reluctant to change or who are ambivalent about changing their behaviour. A systematic review and meta-analysis of RCTs shows that MI outperforms traditional advice giving in the treatment of a range of behavioural problems and diseases [26]. More recently, a pilot study has shown the effectiveness of telephone administered MI to reduce risky sexual behaviour in HIV infected rural populations [27].

The study will examine whether a two-session, telephone administered augmented motivational interviewing intervention based on the IMB model reduces risky sexual behaviour (compared with 'treatment as usual'), in MSM prescribed PEP treatment after potential sexual exposure to HIV. Evidence suggests that the Information-Motivation-Behavioral Skills (IMB) approach could be used to explain sexual risk taking behaviour [28]. This model proposes that information relevant to the personal practice of preventive behaviour, motivation to practice prevention and behavioural skills for practicing prevention effectively, are fundamental determinants of HIV/STI preventive behaviour [29].

The Information, Motivation and Behavioural skills (IMB) model proposes an intervention development process involving (1) elicitation of client resources and needs and, (2) matching intervention content to existing need and behaviour change objectives, (3) implementation of information, motivation and skill development techniques interventions according to protocol and, finally, (4) evaluation. This approach has been found to be effective in changing risky sexual behaviour among HIV negative and infected individuals in more than 25 studies (see [8] for a review) and in changing levels of adherence behaviour amongst people with HIV [9, 10].

## Methods

### Study design

Parallel group randomised controlled trial.

### Participants

*Eligibility criteria:* Participants will be MSM, aged  $\geq 16$  years, prescribed PEP after sexual exposure, and attending a Genito-urinary Medicine (GUM) clinic who are willing and able to give written, informed consent.

*Exclusion criteria:* The following groups of patients will be excluded: people who have received previous psychological support from a clinical psychologist in relation to their risk taking; people with learning difficulties; or unable to read study materials; or with no means of communication acceptable to the patient; or who are seeking PEP after sexual assault.

### Recruitment procedure

The data collection plan is tailored to the standard patient care protocols stipulated in the BASHH guidelines for PEP, and the clinical processes in use at the recruitment sites. PEP is available from GUM or via Accident & Emergency (A&E). Patients are routinely prescribed a 5-day course of PEP medication at general GUM clinics, or at A&E departments outside of GUM hours. Patient access routes then merge at dedicated PEP clinics at GUM within 5 days of initial prescription. Recruiting at the GUM clinic will ensure all patients who are prescribed the full course of PEP (28 days) are included in the trial from either access route. Eligible participants will be identified by a research nurse/ health advisor at the GUM clinic and given study information and consent forms.

Participants will have a 2-week window in which to consent and return baseline measures. This two week period allows the recruitment of patients at an early stage in their prescription, but at a time when their immediate anxiety should be reduced and they are able to give considered, informed consent.

### Baseline and follow-up assessments

Participants enrolled into the study will be asked to self-complete a questionnaire at four time points during the study (at 0,3,6,12 months). The baseline questionnaire will be administered at the recruitment stage, and upon receiving the consent forms and baseline assessments, participants will be randomly allocated to either intervention or control conditions (see randomisation section).

The second questionnaire will be posted to patients or accessed via email/the internet (as per consent) prior to their 3-month follow-up appointment with the clinic. Any patients who have not returned completed questionnaires before their '3-month' follow-up will be sent repeat copies (as per consent), and subsequently called on the telephone (if consented), and finally, may be approached by study staff at their clinic appointment.

The third questionnaire will be posted to patients or accessed via email/the internet (as per consent) 6 months after the end of PEP. Patients not returning their questionnaires will be sent repeat copies, and subsequently called on the telephone (as per consent). Those with a '6-month' follow-up appointment (depending on the recruitment site) and who have failed to return their questionnaire will be approached by study staff at their clinic appointment.

---

 Maximum of 2 repeat copies and 1 text/call/email if consented by patient.

The fourth questionnaire will be posted to patients or accessed via email/the internet (as per consent) 12 months after the end of PEP. Repeat copies, and subsequent telephone calls, will be used as reminders.

The recruitment period is for 12 months to allow sufficient numbers of participants to be recruited. A sample size of 250 (allowing for a 75% recruitment rate and 50% retention rate) is achievable within the time-frame and we anticipate that numbers will be higher given the increasing trends for PEP requests.

### **Randomization and blinding**

The random allocation sequence will be computer generated in advance of the trial. Participants will be randomised after consent and collection of baseline measures. The recruiting staff will not have access to the results of randomisation prior to recruiting the participant. AP will be given the results of the randomisation on a case by case basis by a custodian who is unconnected to the project. Randomisation will occur within each clinic. A statistician (MH) will generate the allocation sequence (who will be blind to the identity of the individuals involved). This is a single-blind trial, given the nature of the behavioural intervention, blinding of participants is not feasible and the interventionist (AP) will know that all those he contacts are in the intervention arm. The PI and statistician will be blind to individual results during the trial and the allocation-to-trial-arm coding will be revealed when the dataset is sealed.

The interventionist (AP) and AP's supervisors will be blind to the baseline and follow-up measures which will not inform the delivery of the intervention. Anonymised measures will be entered onto the database by a person unconnected to the project.

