## **Analyses plan and power calculation**

For the analysis of main effects for the primary outcome a mixed-design ANCOVA will be used with one between-groups factor (treatment vs. control) and one within-groups factor (baseline, 3-, 6- and 12-month measures). For this analysis the estimated effect size is  $f=0.2$  (based on a moderate estimate of effect size from a meta-analysis [24] of one to one interventions to reduce UAI in MSM). 90% power at 0.05 level of significance requires a sample of 250 (125 in each arm). Secondary outcomes will be analysed for the same effect size but with significance adjusted to 0.01 and power to 80%.

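### Allocation is made clinic by clinic, but the stated primary model has no clinic term: a small and avoidable loss of precision, conservative in direction

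*Protocol*

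**What the plan says.** The protocol's section on randomization and blinding states that "Randomisation will occur within each clinic". More than one clinic is involved: the recruitment procedure refers to "the clinical processes in use at the recruitment sites". The number of clinics is not given, and nothing is said about blocking or any other means of balancing the arms within a clinic.

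In the section on the analysis plan and power calculation, "a mixed-design ANCOVA will be used" for the primary outcome, with "one between-groups factor (treatment vs. control) and one within-groups factor (baseline, 3-, 6- and 12-month measures"). It is called an ANCOVA, but no covariate is listed, and clinic appears neither as a factor nor as a covariate. The same section gives an effect size of f = 0.2 and states that "90% power at 0.05 level of significance requires a sample of 250 (125 in each arm").

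**The concern.** A factor used to organise the randomisation normally belongs in the analysis. Where the arms are balanced within clinic, differences between clinics cannot contribute to the difference between arms. A model without clinic still counts those differences as residual variation. Its standard error is then larger than the true one, its intervals are too wide and its test rejects too seldom.

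The protocol does more than stay silent here. It counts the between-groups factors and stops at one. What is at stake is efficiency and agreement between design and analysis, not bias or false-positive findings. There is also a point of pre-specification: an adjusted and an unadjusted analysis could each be presented as the protocol's analysis of an ANCOVA whose covariates are not named.

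**Working it through.** **Inputs from the protocol.** f = 0.2, which for two equal groups is d = 2f = 0.4; N = 250, 125 per arm; alpha 0.05. Sidedness is not stated, so two-sided is assumed.

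**Input assumed.** The share s of total outcome variance that lies between clinics. The protocol gives no figure, so 2%, 5% and 10% are used.

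**Step 1: the protocol's own figure.** With the total SD set to 1, the standard error of the difference is √(4/250) = 0.1265, and 0.4/0.1265 = 3.162. Power is Φ(3.162 − 1.960) = Φ(1.202) = 88.5%. A noncentral F calculation gives 88.3%. This is close to the stated 90%; exactly 90% by the normal formula needs 132 per arm. This calculation treats the comparison as two means at one time point, so what follows applies to the between-groups main effect.

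**Step 2: arms balanced within clinic.** The true variance of the difference is 4(1 − s)/N, while the model without clinic uses 4/N. Hence:

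- overstatement of the standard error: 1/√(1 − s) − 1
- type I error without clinic: 2 × [1 − Φ(1.960/√(1 − s))]
- power without clinic: Φ((3.162 − 1.960)/√(1 − s))
- power with clinic: Φ(3.162/√(1 − s) − 1.960)

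For s = 5%, √0.95 = 0.9747. Type I error is 2 × [1 − Φ(2.011)] = 4.4%. Power is Φ(1.233) = 89.1% without clinic and Φ(1.284) = 90.1% with it.

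| Clinic share (assumed) | SE too large by | Type I error without clinic | Power without clinic | Power with clinic | Gain in points (before rounding) |
|---|---|---|---|---|---|
| 0% | 0.0% | 5.0% | 88.5% | 88.5% | 0.0 |
| 2% | 1.0% | 4.8% | 88.8% | 89.1% | 0.4 |
| 5% | 2.6% | 4.4% | 89.1% | 90.1% | 0.9 |
| 10% | 5.4% | 3.9% | 89.7% | 91.5% | 1.8 |

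**Step 3: simple randomisation within clinic.** Clinic differences now enter the comparison by chance, and the unadjusted variance 4/N is correct. Type I error is 5% and power stays at 88.5% whatever s is. Adjustment would bring power close to the values in the table's power-with-clinic column, less a little for chance imbalance. At s = 10% the gain is thus at most about 91.5 − 88.5 = 3.0 points.

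**Step 4: the arm-by-time test.** Its error term is within-subject variation. A clinic difference that is the same at every time point is absorbed by the subject effects, so leaving clinic out does not enlarge the standard error of that test.

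**The case against.** The strongest reply is that a list of model terms is commonly left to the statistical analysis plan, which is not at hand. An ANCOVA with no named covariate is visibly incomplete, and describing one between-groups and one within-groups factor may only set out the factorial layout. That stands as a reason for modest wording: clinic may have been intended. It does not remove the point, because the protocol states a model and the stated model lacks the stratum.

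Three stronger readings are tempting, and the protocol does not support them.

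- *The standard error is too large.* A reader might infer this as a fact. It needs balance within clinic, and blocking is not mentioned; it needs clinic to predict risk behaviour, and no between-clinic variance is given. The follow-up section says that having a 6-month appointment depends on the site, but that concerns how missing questionnaires are chased, not differences in outcome. The project aims give PEP awareness of 59% in the South East Coast and 70% in London, which is regional survey data and likewise not an outcome difference between clinics.
- *The trial loses planned power.* It does not. Under balance, every power without clinic in the table is at or above the 88.5% that the protocol's own inputs give; under simple randomisation it equals that figure.
- *The omission affects every test of the intervention.* It does not reach the arm-by-time test when the clinic effect is constant over time. The protocol does speak of main effects, so the between-groups reading is open, but it is not the only one.

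**Conclusion.** The mismatch between design and stated model is real; its consequence is small and conditional. For clinic shares of 2% to 10%, and with arms balanced within clinic, the main-effect test runs at about 4.8% down to 3.9% instead of 5%, and adjustment would gain about 0.4 to 1.8 points of power at 250 participants. Without balance the test is valid and only precision is forgone. The error is conservative in either case and does not threaten the validity of a positive result.

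These sizes rest on a two-sided test, d = 0.4 on the total SD, 250 participants analysed, and clinic shares that are assumed. The analysed number may be lower: the follow-up section has "A sample size of 250 (allowing for a 75% recruitment rate and 50% retention rate) is achievable", which leaves unclear whether 250 is before or after losses. If only 125 were analysed, the same formulas give 61.2% against 63.1% at a 5% share and 61.4% against 65.4% at 10%. Retention would then matter far more for power than the clinic term.

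**What to change.** In the protocol's section on the analysis plan and power calculation, name clinic, as the randomisation stratum, as a fixed between-groups factor in the primary model and in the corresponding secondary models. Leave the handling of baseline as it stands: it is already a level of the time factor, and adding it as a covariate as well would be a different model and a separate decision.

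The cost is one phrase and one degree of freedom for each clinic beyond the first. The number of clinics is not stated, so calling this a few degrees of freedom assumes that they are few; against 250 − 2 = 248 residual degrees of freedom it is then negligible. The change is worthwhile with or without blocking, and it should be made before the allocation coding is revealed. The sample size need not change.

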### **Trial treatment arms**

#### **Control group: Treatment/management as usual**

Both of the groups will receive 'treatment/management as usual': Patients are initially seen by a HA/SpN for an initial consultation, 5 day prescription of PEP and blood tests (for HIV, Hepatitis B and liver function). Patients receive their first follow-up appointment 5 days later to receive further PEP (if HIV-ve). After the 28 day treatment regimen patients receive either a face-to-face or telephone appointment with the HA/SpN to discuss their sexual health, adherence to PEP and the blood test results. At 4 months after exposure (3 months after the end of PEP) patients are recalled by the HA for HIV testing. In order to assess the impact of the intervention on outcome measures and IMB constructs, those allocated to control group 1 will be asked to complete all measures at 0,3,6, and 12 months.

### **Intervention group**

#### **Procedure**

The intervention group will receive 'treatment and management as usual' plus the addition of an intervention which will be delivered as two telephone sessions employing motivational interviewing (MI) augmented with information and skills building based on the IMB model of behaviour change. The first call will be made within one week of the participant being consented into the trial and after baseline assessments are received. The second call will occur 7 days (+/-2 days) later. The intervention will be completed by the end of the 28 day course of PEP. A telephone format is proposed to allow the same person to conduct all interventional sessions to control for provider differences and to facilitate recruitment from a wide geographical area in an economical manner. If shown to be effective, this intervention would be sustainable within an improved routine care model.

### **Duration and content of intervention**

**Telephone delivered MI**

Each telephone session will be a maximum of 30 minutes long. The second session will contain similar content to the first but will reiterate and build on the risk reduction motivation from session 1. In the case of drop-out between the 2 intervention sessions, a dose-response can then be assessed.

The interventionist will initially assess individual risk behaviours and any informational, motivational or skill deficits which have contributed to maintenance of participants' risky sexual behaviours and discuss particular areas related to risky sex e.g. the use of alcohol or drugs during sex. The interventionist will elicit self-motivational statements from the participant with the use of open-ended questions and will utilise MI strategies to increase motivation to change, including:

- 1) Providing the participant with feedback about his risky sexual behaviours
- 2) Increasing the participant's sense of responsibility to reduce risky sexual behaviours
- 3) Providing brief and direct advice to create a desire for change
- 4) Providing a menu of options from which the participant can choose to reduce risk
- 5) Demonstrating empathy by listening carefully, and accurately understanding his problems
- 6) Enhancing self-efficacy to reduce risky sexual behaviours [31]

If an individual discontinues with PEP before the end of the treatment, they will still be eligible to continue in the study. Data on adherence will be captured by the measures and a review of the medical notes.

